#### Statistical analysis

The results will be presented in accordance with the CONSORT 2010 recommendations. Estimates of the primary and secondary endpoints incidence will be provided with their 95 % confidence interval.

The primary analysis will be done on an intention to treat basis, in all patients included in the trial and having undergone randomization.

Incidence of the unadjusted composite endpoint will be compared between the two groups using a Chi-square test. A multiple logistic regression model will compare the effects adjusted for LCOS prognostic factors: type of surgery performed (CABG alone, or combined surgery), LVEF (<30 %, or between 30 and 40 %), redo nature of the surgery, preoperative treatment with inotropic drugs or mechanical assist device and presence of preoperative beta-blocker therapy.

Three subgroups analyses are planned. They will assess whether the levosimendan effect varies according to:Type of surgical procedure performed (CABG alone or combined surgery)LVEF <30 %, or 30 % ≤ LVEF ≤ 40 %Presence of a preoperative treatment with beta-blockers.

The heterogeneity of the treatment effect will be evaluated by an interaction test and presented using a forest plot [16].

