### Randomization and blinding procedures

The allocation of treatments will be performed by minimization (deterministic dynamic allocation) [14]. The procedure will take into account the center, the surgery performed (CABG alone, or combined surgery), LVEF (<30 %, or between 30 and 40 %), the redo nature of the surgery, the existence of a treatment by preoperative inotropic agents or IABP, and the existence of preoperative beta-blocker therapy. It will balance the distribution of prognostic factors between the two groups and within each center. We will introduce a random component to reduce the predictability of the allocation.

We chose to use a minimization procedure because the stratified randomization is not effective in trials with small sample size and large number of strata. This is the case in the present study since the 3 factors that must be controlled (type of surgery, preoperative treatment, and LVEF range) would result in eight strata at all 13 centers.

The randomization algorithm will be established by an independent statistician. This algorithm will then be installed on a website with secure access. At randomization, the clinician will obtain the blinded patient allocation number after having provided the patient characteristics required by the algorithm. The result of the randomization will be sent to the pharmacy at the center involved.

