### Statistics

#### Number of subjects required

The number of subjects required is 340 patients (170 per group). This sample size has been obtained using the Nquery Advisor statistical software according to the following assumptions:Incidence of the composite endpoint in the control group 65 % (proportion estimated from our personal data);Incidence of the composite endpoint in the levosimendan group 50 %. According to Levin et al. [15], postoperative administration of levosimendan in patients having a LCOS has reduced by 28 % the use of an additional inotropic drug and by 12 % the use of a mechanical assist device, compared to dobutamine.Alpha risk of 5 % and power of 80 %.

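### The primary chi-square ignores the six factors used in the minimisation, and the adjusted model leaves out centre; the test is conservative and forgoes roughly 0 to 6 points of power

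*Protocol article*

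**What the plan says.** **Allocation** (Randomization and blinding procedures). Treatment is assigned by minimisation with a random component. "The procedure will take into account the center, the surgery performed" and four further items: LVEF below 30 % or 30 to 40 %, redo surgery, "the existence of a treatment by preoperative inotropic agents or IABP", and preoperative beta-blocker therapy. The stated purpose is balance between the groups and inside each centre.

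**Analysis** (Statistical analysis). "Incidence of the unadjusted composite endpoint will be compared between the two groups using a Chi-square test". A multiple logistic regression follows, adjusted for type of surgery, LVEF class, redo surgery, and "preoperative treatment with inotropic drugs or mechanical assist device and presence of preoperative beta-blocker therapy". Centre is not in that list. The section does not say in words which of the two comparisons decides. The chi-square comes first, and the sample size matches it.

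**Sample size** (Number of subjects required). "Incidence of the composite endpoint in the control group 65" %; "Incidence of the composite endpoint in the levosimendan group 50" %; "Alpha risk of 5 % and power of 80" %; 170 patients per group, 340 in all.

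**The concern.** Minimisation removes most of the chance difference between arms on the factors it balances. When those factors are prognostic, the estimated treatment difference varies less from trial to trial than it would under simple randomisation. The chi-square test does not know this: its variance still contains the part that the design has taken out. Its p-values are then too large on average and its real type I error falls below 5 %. The article itself calls the five patient-level factors prognostic for LCOS, so some effect is to be expected.

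The planned logistic model corrects this only in part, because centre is balanced at allocation and then left out.

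There is also a smaller inconsistency. Allocation codes preoperative support as inotropes or IABP; the model codes it as inotropes or a mechanical assist device. The Study population section admits patients who have another left ventricular assist device in place. Such a patient, with neither inotropes nor IABP, would be a no at allocation and a yes in the model.

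At stake is efficiency: balance obtained at randomisation that the primary test does not use.

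**Working it through.** **1. The plan's own figure.** Inputs from Number of subjects required: p₁ = 0.65, p₂ = 0.50, alpha 5 %, power 80 %. Sidedness is not stated; two-sided is assumed. Mean rate 0.575.

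n per arm = [1.960·√(2·0.575·0.425) + 0.8416·√(0.65·0.35 + 0.50·0.50)]² / 0.15²
= [1.3702 + 0.5816]² / 0.0225 = 3.8095 / 0.0225 = 169.3, rounded up to 170.

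Power at 170 per arm is 80.2 %. The stated size is reproduced exactly by the plain two-proportion test without continuity correction. (With continuity correction it would be 183 per arm; one-sided, 134.)

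**2. Why the chi-square is conservative.** Write R² for the share of outcome variance that the balanced factors explain and the allocation effectively removes. The true variance of the difference is then about (1 − R²) times what the chi-square assumes, and its real type I error is about 2·Φ(−1.96/√(1 − R²)). It equals 5 % only if R² = 0.

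**3. Size, by simulation of the planned allocation.** About 6,000 trials per cell.

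- From the article: 340 patients, 13 centres (340/13 ≈ 26 each), the six factors, 65 % against 50 %. Under the null both arms were set to 65 %.
- Assumed, because the article gives no values: probability 0.8 of following the minimisation; unequal centre sizes; prevalences of 30 % combined surgery, 35 % LVEF < 30 %, 8 % redo, 15 % inotropes/IABP and 70 % beta-blocker.
- Three assumed effect levels (absolute log-odds ratios of the factors; between-centre SD on the logit scale): weak (0.1–0.4; 0.2), moderate (0.3–1.0; 0.5), strong (0.5–1.8; 0.9).

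Each trial was tested by the chi-square, by a linear risk-difference model with the five listed factors, and by the same model with centre added.

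| | Weak | Moderate | Strong |
|---|---|---|---|
| Type I error, chi-square | 4.9 % | 4.0 % | 3.3 % |
| Type I error, five factors | 4.9 % | 4.5 % | 4.3 % |
| Type I error, five factors + centre | 5.2 % | 4.8 % | 5.2 % |
| Power, chi-square | 80.7 % | 80.4 % | 82.2 % |
| Power, five factors | 80.6 % | 82.0 % | 85.1 % |
| Power, five factors + centre | 80.6 % | 83.1 % | 88.0 % |

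Monte Carlo standard error is about 0.3 points at 5 % (√(0.05·0.95/6,000)) and 0.5 points at 80 %. By the formula in step 2, the chi-square's type I errors correspond to R² of roughly 1 %, 9 % and 15 %.

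Power forgone by the chi-square against full adjustment: 80.6 − 80.7 ≈ 0; 83.1 − 80.4 = 2.7; 88.0 − 82.2 = 5.8 points. Of this, adding centre to the five factors accounts for 0, 1.1 and 2.9 points.

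**4. Choice of adjusted method.** Logistic regression with 12 fixed centre terms, run in a parallel set of trials, gave power of 81.4 %, 84.6 % and 89.4 %, but type I error of 5.5 %, 5.4 % and 5.8 %. Part of that apparent gain is therefore test size, not efficiency.

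**The case against.** The strongest reply is that nothing here invalidates the trial. The sample size was calculated for the plain two-proportion test and is correct for it. Chi-square power stays at or above 80 % in every scenario. The error is on the safe side, so a positive result stands. An adjusted model with all five patient-level factors is already planned and recovers part of the loss. All of this stands.

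It also stands that the size is uncertain. The article gives no factor effects, prevalences or centre heterogeneity, and with weak effects the loss vanishes.

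A reader might infer several stronger things that the document does not support:

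- *The trial is underpowered, or its false-positive rate is wrong in the harmful direction.* The figures above show neither. One qualification: the 80 % holds for the chi-square without continuity correction, the version that reproduces the stated size. With the correction, simulated power was 77 to 79 %.
- *Centre is the dominant predictor of the endpoint.* The components record a need for inotropes, devices or renal replacement, so local practice may matter, but the article offers no evidence of how much.
- *Giving two comparisons without ranking them is an error.* The order and the sample size point to the chi-square, and an analysis plan that is not shown may settle the matter.
- *A logistic odds ratio conflicts with sizing on a 15-point difference.* The article names no effect measure for the decision and promises incidences with confidence intervals, so no error follows.

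**Conclusion.** The point holds as one of efficiency and consistency. The planned primary test ignores the allocation factors, and the written-out adjusted model omits one of them. The direction is firm: the chi-square is conservative to the extent that the factors are prognostic. The size is conditional: type I error of about 4.9 %, 4.0 % or 3.3 %, and about 0, 3 or 6 points of power forgone, under weak, moderate or strong effects that are assumed throughout. The planned power is met and type I error is not inflated. The mismatch in the preoperative-support factor is real but small. It touches only patients with a non-IABP device and no inotropes or IABP, a number the article does not give.

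**What to change.** Name as the primary analysis a comparison of the composite endpoint adjusted for all six minimisation factors, reported as an adjusted risk difference with 95 % confidence interval. Keep the chi-square as a sensitivity analysis.

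Handle centre by a method suited to about 26 patients per centre, for example a random effect or a linear or standardised risk difference, and avoid 12 fixed terms in a logistic model. The linear model kept type I error at 4.8 to 5.2 % in the simulations. A random effect and standardisation were not simulated here and should be checked the same way before either is fixed.

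In the model, use the preoperative-support factor as it was coded at allocation (inotropes or IABP).

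Cost: for these changes, analysis wording only. No more patients are needed, and all six factors are already entered at randomisation. If the sponsor prefers to count any mechanical device in both places, the minimisation specification must change too. That alters the allocation algorithm and the data entered at randomisation, so it is more than a wording change.

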## Discussion

### Rationale for levosimendan in cardiac surgical patients with poor LV function

Levosimendan was introduced a few years ago and was initially approved in some countries for the management of acutely decompensated heart failure following the results of two multicenter randomized controlled trials (LIDO and SURVIVE) [17, 18]. Preliminary data on the beneficial effects of levosimendan in cardiac surgical patients has been reported in several studies [7–9, 15, 19–24]. However, this data was obtained from trials conducted at single centers [8, 19–24], on small cohorts (<100 patients) [8, 9, 20–22, 24], without randomization [24], or according to a single-blinded protocol [7, 9, 15, 22–24]. Therefore, the level of evidence supporting the beneficial effect of levosimendan is not very strong.

In a small randomized study, patients with a preoperative LVEF ≤30 % treated with levosimendan received a smaller amount of dobutamine in comparison to those treated with milrinone and had a lower mortality rate after surgery [9]. In another prospective, randomized, double-blind study comparing levosimendan to a placebo in 60 patients with a preoperative LVEF <50 % undergoing CABG, levosimendan was found to enhance primary weaning from cardiopulmonary bypass in comparison to the placebo [8]. Levin et al. compared preoperative levosimendan versus placebo in 252 CABG patients with a LVEF <25 % and found that levosimendan reduced mortality (3.9 vs 12.8 %; *p* < 0.05), the incidence of LCOS (7.1 vs 20.8 %; *p* < 0.05) and of complicated weaning from cardiac pulmonary bypass (2.4 vs 9.6 %; *p* < 0.05). Compared to the placebo group, the levosimendan-treated patients also required less inotropes (7.9 vs 58.4 %; *p* < 0.05), vasopressors (14.2 vs 45.6 %; *p* < 0.05), and intra-aortic balloon pumping (6.3 vs 30.4 %; *p* < 0.05) [7]. A recent meta-analysis of perioperative use of levosimendan confirmed that the efficacy of levosimendan seems to be more pronounced in patients with preoperative left ventricular dysfunction [12].

### Study population

In addition to CABG surgery, we deliberately choose to enrol patients undergoing combined surgery despite the fact that they might introduce some variability in our population. Indeed, a patient with aortic stenosis and poor left ventricular function associated with coronary artery disease is likely to have a myocardial dysfunction related to the long lasting pressure overload in addition to myocardial ischemia. Ischemic mitral insufficiency combines chronic volume overload and ischemia, and the correction of mitral regurgitation (valve repair or replacement) will adversely affect left ventricular afterload. Furthermore, these combined procedures are inherently associated with longer aortic cross-clamping times which, in turn, may increase the probability of a LCOS, as reflected by the higher mortality rate in this population [25]. We have no data to determine whether levosimendan is more likely to have beneficial effects in one subgroup or another. The cardio protective effect of mitochondrial K_ATP_ channel opening might be more effective in patients with pure ischemic cardiomyopathy. But the vasodilatation resulting from vascular smooth muscle K_ATP_ channel opening and the inotropic effect due to calcium sensitizing of the myofilaments are expected to be beneficial regardless of the mechanism of LV failure. The respective importance of each pharmacologic effect of levosimendan is not clearly identified. The minimization process used for randomization takes into account the fact that CABG is isolated or combined with a valve repair and should help in addressing this question of the efficacy of the drug in relation to the underlying type of pathology. Another reason for being “less selective” is to facilitate recruitment and to maximize the number of eligible patients over a relatively short period of time. This is an important issue as levosimendan must be used within 24 months after production. Broadening of inclusion criteria is also likely to generate outcome data more reliably representative of current practice in the “real world”.

### Pharmacokinetics of levosimendan

Levosimendan has a linear pharmacokinetic profile with an elimination half-life of about one hour. Maximum plasma levosimendan concentration is reached 4.4 h after an infusion of 0.2 μg/kg/min over 6 h. Maximum plasma concentration of its main metabolite (OR-1896) is reached 2–5 days after an infusion of 0.2 μg/kg/min over 24 h. Since OR-1896 has a similar haemodynamic profile to levosimendan itself, this explains the prolonged effect of the drug. Levosimendan is extensively metabolized by the liver and inactive metabolites are excreted in the urine and the faeces within 24 h [26]. For patients with renal impairment, defined as a glomerular filtration rate between 30 and 60 mL/min/1.73 m^2^, the dose of levosimendan does not need to be reduced and the drug even seems to improve kidney function in patients with acute decompensated heart failure [27]. Interestingly, the beneficial haemodynamic effects of levosimendan, unlike those of dobutamine, are not attenuated by the concomitant use of β-blockers [18].

### Side effects of levosimendan and safety issues

According to the clinical data of REVIVE II and SURVIVE trials, moderate hypotension (mean reduction in systolic blood pressure: −4 mmHg, and diastolic blood pressure: − 6 mmHg) was the most frequent adverse event observed after a bolus infusion of levosimendan (12 μg/kg) and lasted for 12 h [17, 28]. In the SURVIVE trial, the occurrence of hypotension did not differ between the levosimendan and dobutamine groups. However, based on this finding we will not administer any bolus of levosimendan in our patients in order to reduce the risk of intra-operative hypotension. Previous authors using a continuous infusion of levosimendan without a loading dose observed beneficial effects without hypotension [9, 22, 24]. Moreover, 2012 European Society of Cardiology guidelines for the diagnosis and treatment of acute and chronic heart failure recommended the use of levosimendan without a loading dose for hypotensive patients [29].

Levosimendan administration has also been associated with a higher incidence of atrial fibrillation in comparison to a placebo (9 vs 2 %) [28] or dobutamine (9 vs 6 %) [17] in trials involving patients with left ventricular failure. In contrast, meta-analysis of studies involving surgical patients suggested a reduced incidence of atrial fibrillation in the group of patients treated with levosimendan [30]. We will collect information on the incidence of atrial fibrillation in our patients to try to provide new insight regarding these discrepant results. Atrial fibrillation detection will rely on continuous electrocardiography monitoring while in ICU, and on clinically patent arrhythmia episodes leading to 12-lead electrocardiography recording while in the ward. Information regarding other arrhythmias (ventricular tachycardia, ventricular fibrillation, torsade de pointe) will also be collected to assess the safety profile of levosimendan in the perioperative period.

Perioperative ischemia is a major concern after CABG surgery. The safety profile of levosimendan regarding the myocardial oxygen balance seems favourable in comparison to dobutamine. Previous studies involving CABG patients suggested that postoperative ischemia was less frequent in levosimendan-treated patients with respect to a placebo [7, 19]. Peak postoperative troponin I (between Day 1 and Day 2), measured by highly-sensitive troponin assay will be monitored at each center to assess myocardial damage [31].

## Conclusion

This trial is intended to answer an important question: is there a role for levosimendan as a pre-treatment for patients with poor left ventricular function (LVEF ≤40 %) undergoing CABG (alone or combined with valve surgery) under cardiopulmonary bypass? The primary objective of the study is to quantify the occurrence of simple clinical markers of low cardiac output syndrome in the levosimendan and placebo groups. If levosimendan proves superior to a placebo, this will result in a change of management for high risk cardiac surgical patients, which is clinically relevant in view of the increased prevalence of this patient cohort.

## Abbreviations

CABG, coronary artery bypass grafting; CONSORT, Consolidated Standards of Reporting Trials; CRF, case report forms; IABP, intra-aortic balloon pump; ICU, intensive care unit; LCOS, low cardiac output syndrome; LVEF, left ventricular ejection fraction; MAP, mean arterial pressure; RRT, renal replacement therapy
